### Randomization, blinding, and code-breaking

Eligible patients (*n* = 36) will go through assessments at baseline and will be randomly allocated to 2 groups, each consisting of 18 participants. Randomization will be done by an independent researcher in the biostatistics platform at the George and Fay Yee Centre for Healthcare Innovation (CHI) at the University of Manitoba. Randomization will be performed using code written in the R statistical programming language (version 3.5.3). Treatments will be assigned with a 1:1 ratio. A total of 48 randomization cards will be prepared, one set of 24 for each sex. The randomization schedule will be transferred into sets of opaque sealed envelopes. After a participant’s baseline visit, the study staff will open a sealed envelope which will contain the participant’s allocation. The order of the interventions will be blinded for both the investigators and the participants. Treatments will be given in sealed sachets; sachet content will be blinded by an outside party, given to the study staff labelled as A or B, and dispensed to participants according to their treatment period. Treatments will not be unblinded until the analyses are complete, unless required due to adverse events during the clinical trial. There will also be a midpoint review of the participants’ clinical data by an independent nephrologist who will be unblinded (see the “Qualified investigator responsibilities” section).

### Sample size calculation

A final samples size of 30 participants in this study will be able to detect a difference between the treatments in total p-cresol sulphate of 17.5 μmol/L, or ~ 15% change, at a power of .88 (alpha = 0.05, two-sided), given a within-person correlation of .79 [23] and an estimated standard deviation of 45 μmol/L [9] for total p-cresol sulphate. A 30% or greater drop in uremic solutes would be considered clinically significant, warranting additional trials investigating this prebiotic intervention in CKD, and we are confident we would be able to detect such a change should it occur. To account for the loss of power due to dropouts, we will recruit 36 participants.

#### Inclusion in analysis

The primary analysis will be conducted using the All Participants (intent-to-treat) analysis set. The primary analysis will be repeated in the *Completers* analysis set. Demographics and all other baseline measurements will be analysed in the All Participants set as well as in the Completers set.

Completers analysis set: all participants who have completed the trial

All Participants analysis set: all randomized participants

### Discontinuation/withdrawal of participants from trial treatment

Each participant has the right to withdraw from the trial at any time. Participants may discontinue trial participation at any time and are requested to contact a research team member to inform them of their decision. In addition, the investigators may discontinue a participant from the trial at any time if the investigators consider it necessary for any reason including pregnancy, ineligibility (either arising during the trial or retrospectively having been overlooked at screening), significant protocol deviation, significant non-compliance with the protocol, disease progression which results in the inability to continue to comply with the protocol, withdrawal of consent, and loss to follow-up.

Withdrawal will not result in the exclusion of the data for that participant from the analysis. As the primary analysis will be based on an intention-to-treat, there will also be a completer only analysis performed.

If a participant is withdrawn within the first 4 weeks of the trial, they will be replaced. If the replacement participant is withdrawn, there will be no subsequent replacement.

The reason for withdrawal will be recorded in the CRF, if provided.

### Remuneration

Participants will be remunerated $200 for each completed period or the prorated value if they withdraw from the trial. Each participant would receive $400 in total if they complete the full trial.

Participant’s name and address will be used for preparing, printing, mailing, and financial record keeping or remuneration cheques. Pre-paid postage and envelope will be provided to the participant with a form requiring their signature upon receipt of the remuneration cheque. Participants will be asked to return the form to CDIC. This record will be kept for a maximum of 7 years.

## Discussion

CKD has been associated with changes in gut microbial ecology, or “dysbiosis”, which may contribute to disease progression. Individuals and animals with CKD exhibit profound alterations in the gut environment including shifts in microbial composition, increased faecal pH, and increased blood levels of gut microbe-derived metabolites. Recent studies have focused on dietary approaches to favourably alter the composition of the gut microbial communities as a treatment method in CKD. Resistant starch (RS), a prebiotic that promotes the proliferation of gut bacteria such as *Bifidobacteria* and *Lactobacilli*, increases the production of metabolites including short-chain fatty acids, which confer a number of health-promoting benefits. Studies from animal models and individuals with CKD show that RS supplementation attenuates the concentrations of uremic retention solutes, including indoxyl sulphate and p-cresol sulphate. The fermentable dietary fibre-high amylose maize-resistant starch type 2 (HAMRS2) has been shown to alter the gut milieu in CKD rat models leading to markedly improved kidney function. RPS, which is a R2-resistant starch, has been shown to increase carbohydrate-degrading bacteria, such as Bifidobacteria, and decrease bacteria with proteolytic activity, such as *E. coli* [14, 17, 18]. RPS has also been shown to reduce the concentrations of gut microbiome-derived uremic toxins in pigs [19]. While animal and human studies involving resistant starch have shown the ability to change the gut microbiota and reduce the amount of uremic toxins, there are limited studies in patients with CKD [14].

In one study conducted in individuals with CKD already on dialysis, a reduction in uremic toxins following high-amylose cornstarch consumption for 6 weeks was observed [20]. High-amylose cornstarch is ~ 60% resistant starch by dry weight, whereas the RPS to be used in this proposal is ~ 70% resistant starch and ~ 10% other dietary fibres [17]. Here, we will conduct a 2-period randomized double-blind cross-over trial to investigate whether the consumption of RPS as an adjunctive therapy to current standards of CKD care will reduce uremic toxins and symptoms by altering gut microbiota in patients with CKD.

The results of this study will add to the evidence for the efficacy of RPS in patients with CKD and will form the basis of a larger multicentre randomized controlled trial testing the effect of RPS on delaying CKD progression and dialysis initiation.

### Data management

#### Source data

Source documents are where data are first recorded and from which participants’ CRF data are obtained. CRF entries will be considered source data if the CRF is the site of the original recording (e.g. there is no other written or electronic record of data). All documents will be stored safely in confidential conditions. On all trial-specific documents, other than the signed consent forms, master list, and remuneration forms, the participant will be referred to by the trial participant code, not by name.

#### Access to data

Direct access will be granted to authorized representatives from the sponsor, the host institution, and the regulatory authorities to permit trial-related monitoring, audits and inspections.

#### Data recording and record keeping

All trial data will be entered from paper CRF or collected via the University of Manitoba REDCap platform, and other source documents will be entered into this REDCap database. The participants will be identified by a unique trial-specific number and/or code in this REDCap database. The participant’s name and any other identifying information will not be included in the REDCap database, except for the signed informed consent form, remuneration form, and study master list. Participants’ home and email addresses and phone numbers will be collected and linked to the study ID and participant name on a physical/electronic study master list which will be used to coordinate trial activities such as home deliveries of the study materials, remuneration cheques, and communication with participants during the trial. This master list will be stored in a locked cabinet at the CDIC or on a password-protected shared drive/computer at CDIC. Participants’ names and addresses will be shared with the delivery staff or couriers during the delivery process, as well as used for mailing remuneration cheques for the participants who do not pick up in person.

Trial data, without identifying participants’ personal information, will be stored in a secure research environment at the University of Manitoba using REDCap. REDCap is implemented locally by the Data Science platform at the George & Fay Yee Centre for Healthcare Innovation at the University of Manitoba. Study virtual visits will be conducted through the University of Manitoba Microsoft Teams platform, which is an externally hosted cloud-based service. Electronic data with identifying participant personal information, such as name and contact information, will be password-protected and stored in an Excel file on a computer at CDIC. Electronic records of signed consent forms will be stored on REDCap, as well as stored in a password-protected secure computer/shared drive at CDIC or in a locked cabinet. Paper signed consent form will be stored in a locked cabinet in CDIC. Other study logs will be organized in a study binder and kept in CDIC. CDIC is secured 24 h per day and has restricted access.

All trial research records will be kept for 25 years. Paper CRFs and source data will be kept in a locked storage container, apart from any personal identifying information at CDIC. Paper files will be disposed of using the confidential document destruction method at CDIC.

Electronic data will be de-identified and retained for 10 years following the end of the study. Electronic data may also be shared in a de-identified form to academic journals for publication purposes. The data may be stored by the academic journal or other open-access repositories under an open-access policy in which case it may be used by other researchers for further data analysis and research purposes. Paper files will be disposed of using the confidential document destruction method.

#### Criteria for the termination of the trial

The trial will be continued until all recruited participants have reached the end of their follow-up and data have been collected, processed, and cleaned. There are no plans for early termination.

#### Procedure for accounting for missing, unused, and spurious data

The number and proportion of missing values will be documented in the clinical study report. Missing values will not be imputed unless otherwise noted. Analyses will exclude data from participants who have missing values for any variable required for the analysis.

When data are observed to be unusual in a way that cannot be explained or ruled to be in error, analyses may be repeated after excluding the record involved. These additional analyses will be presented as sensitivity analyses.

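### Read literally, the missing-data rule drops one-period participants from the primary analysis, which contradicts the intention-to-treat and withdrawal rules and leaves the Completers repeat almost uninformative

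*Protocol article*

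**What the plan says.** Three parts of the protocol article bear on who enters the primary analysis.

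- **Inclusion in analysis.** "The primary analysis will be conducted using the All Participants (intent-to-treat) analysis set", and that set is defined by "All Participants analysis set: all randomized participants". Then "The primary analysis will be repeated in the" Completers set, defined by "Completers analysis set: all participants who have completed the trial".
- **Discontinuation/withdrawal of participants from trial treatment.** "Withdrawal will not result in the exclusion of the data for that participant from the analysis". The section adds that a completers-only analysis accompanies the intention-to-treat analysis.
- **Procedure for accounting for missing, unused, and spurious data.** "Missing values will not be imputed unless otherwise noted", followed by "Analyses will exclude data from participants who have missing values for any variable required for the analysis". No exception is noted for the primary outcome.

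Under Statistical analysis, end-of-period outcomes are modelled with SAS MIXED. Sequence and sex are fixed factors and participant is the repeated factor. The Sample size calculation recruits 36 so that 30 remain.

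**The concern.** The rules cannot all be followed for a participant who completes period 1, has serum drawn at its end, and leaves before the end of period 2. The withdrawal section keeps the period-1 value. The missing-data section removes the participant, because a value that the two-period comparison uses is absent.

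If the missing-data rule prevails, the analysis labelled intention-to-treat is in effect a complete-case analysis. The repeat in Completers is the only check on dropout that the article states, and it would then be run on nearly the same people. Outcome-related dropout is plausible here: participants have an eGFR below 15 mL/min/1.73 m², and the withdrawal section itself lists disease progression and non-compliance as reasons for discontinuation.

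**Working it through.** **1. The plan's own figure.** Inputs from the Sample size calculation: difference 17.5 μmol/L, SD 45, within-person correlation 0.79, two-sided alpha 0.05, final n = 30.

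- SD of the within-person difference = 45 × √(2 × (1 − 0.79)) = 29.16
- Standardized effect = 17.5 / 29.16 = 0.600
- Noncentral t power at n = 30: 0.888 (29 df) or 0.887 (28 df)

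The stated 0.88 is reproduced. Recruitment also agrees: 30 / (1 − 1/6) = 36, so the allowance is 6 of 36, or 16.7%.

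**2. Who is analysed at the planned loss.** Assume all six losses occur before the end of period 2.

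| Rule applied | Members of the primary analysis |
|---|---|
| Inclusion and withdrawal sections | All 36 randomized, as far as they have an end-of-period value |
| Missing-data section, literal | The 30 with both end-of-period values |
| Completers repeat | The 30 who finish, less any without a serum result |

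The second and third rows differ only through a completer whose serum result is missing.

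**3. Effect on power.** The treatment effect was estimated by generalized least squares with covariance V = 45² × [[1, 0.79], [0.79, 1]]. Each complete pair adds X′V⁻¹X to the information; each period-1-only participant adds x′x / 45². Power = Φ(17.5 / SE − 1.96). For example, with 30 pairs SE = 29.16 / √30 = 5.324, and Φ(3.287 − 1.96) = 0.908. This normal approximation runs slightly above the t-based 0.888, so only the change matters. It is assumed that every lost participant supplied a period-1 value. Ranges are with and without a sequence term.

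| Lost of 36 | SE, pairs only | SE, period 1 kept | Power, pairs only | Power, period 1 kept |
|---|---|---|---|---|
| 6 (planned) | 5.324 | 5.269–5.278 | 0.908 | 0.912–0.913 |
| 9 (assumed) | 5.612 | 5.517–5.538 | 0.877 | 0.885–0.887 |
| 12 (assumed) | 5.953 | 5.803–5.848 | 0.836 | 0.849–0.854 |

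The gain is about 0.5 to 2 percentage points. It is small because a one-period participant contributes only between-person information.

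**4. Effect on bias.** Crossovers were simulated with a true effect of −17.5 and about 18% dropout after period 1, made more likely by a higher observed period-1 value. The logistic form and its slopes are assumptions.

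- In 6,000 trials per setting, with slopes of 0.5, 1 and 2 per SD and a period drift of 10 μmol/L, complete-case means were −17.39, −17.24 and −17.21 (Monte Carlo SE 0.07). The shortfalls are 0.11, 0.26 and 0.29.
- In 4,000 trials per setting, complete-case estimates lay 0.17 to 0.44 μmol/L closer to zero than available-data estimates (paired SE below 0.02).

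The largest of these, 0.44, is 0.44 / 17.5 = 2.5% of the target difference and 0.44 / 5.32 = 0.08 of a standard error. The within-person contrast cancels most of the selection on level.

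**The case against.** The best defence is that the missing-data sentence is a general rule and the withdrawal sentence a specific one, so the specific one governs. SAS MIXED does not need both periods from each participant, so which variables are required is open. On that reading the general rule means little more than no imputation, and an analysis plan that is not shown may say so.

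That reading is possible, but nothing in the article states it, and the wording leans the other way. The exclusion sentence takes the participant as its unit, while the next paragraph, on unusual values, speaks of the record. The sample size section also treats dropouts as contributing nothing. This is a conflict between stated rules, not a detail left to another document.

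Other parts of the defence stand, and they rule out stronger readings that a reader might infer:

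- **Any missing value deletes the participant.** The rule covers only variables required for the analysis in question. A missing questionnaire or stool sample removes nobody from the toxin analysis.
- **The two sets are identical.** Completers are defined by finishing the trial, not by having serum results. Withdrawals in the first 4 weeks are also replaced, so the counts need not be exactly 36 and 30.
- **The discontinuation clause makes it worse.** That "the investigators may discontinue a participant from the trial at any time if the investigators consider it necessary for any reason" is a common provision and does not show the missing-data rule to be wrong. Whether sampling should continue after product is stopped is a separate design question.

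**Conclusion.** The contradiction is real and concerns the population of the primary analysis. Taken literally, the missing-data rule leaves the intention-to-treat analysis with essentially the Completers' membership, about 30 of 36 at the planned loss, and the planned repeat then carries almost no information about dropout.

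A reader might infer that the treatment estimate is seriously biased or the trial underpowered. The figures do not support that: about 0.5 to 2 power points, and a few tenths of a μmol/L at most on 17.5. These figures rest on the protocol's SD and correlation, on lost participants having given a period-1 value, and on dropout driven by that observed value. If dropout depends on unobserved values, the bias is not bounded by this work; but the same holds for a mixed model that assumes missing at random, so it is no argument for one approach over the other.

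The point should be fixed because it is cheap and removes an inconsistency. In a trial that calls itself exploratory, it is not a critical defect.

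**What to change.** In the section on missing, unused and spurious data, replace the exclusion sentence, for the mixed-model analyses, with:

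> All available end-of-period values from all randomized participants enter the mixed model (REML, valid under missing at random); no participant is excluded because one period's value is missing.

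Keep Completers as the sensitivity analysis. Its comparison with the primary result then shows what the one-period participants change. Those who leave before any end-of-period sample still contribute no outcome, so the report should give their number by sequence.

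The cost is one sentence. The procedure is the one already named, and no visit, sample or added sample size is needed. The change should be made before unblinding.

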#### Procedures for reporting any deviation(s) from the original statistical plan

All protocol deviations documented in the clinical trial database will be tabulated (if appropriate) and listed in the clinical study report.

#### Recording of adverse events

Given the nature of the intervention, it is very unlikely that any adverse events will be related to the trial. However, all AEs occurring during the trial that are observed by the investigators or reported by the participant will be recorded on the CRF, whether or not attributed to the trial intervention.

The following information will be recorded: description, date of onset and end date, severity, and assessment of relatedness to trial intervention. Follow-up information should be provided as necessary. In case any adverse event is reported, patients will be offered to be seen in the next available clinic visit or within 1 week, whichever is earlier, and will continue to be followed in the clinic until the AE is resolved.

The severity of events will be assessed on the following scale: 1 = mild, 2 = moderate, and 3 = severe.

AEs considered related to the trial intervention as judged by the qualified investigator will be followed either until resolution or the event is considered stable. In case AEs result in withdrawal from the trial, the patients that are withdrawn due to adverse treatment reaction will also be followed by the CKD clinic until the AEs has resolved.

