**Fig. 1 Fig1:**
[figure not shown]
Study protocol flow chart

Participants will consent to follow a 26-week study regimen. Each participant will receive 2 sachets per day containing either 15 g of RPS (MSPrebiotic, resistant potato starch treatment) or 15 g cornstarch (Amioca TF, digestible starch control). The powder in the sachets will be mixed in water and consumed, one sachet in the morning and one before bed. Participants will be instructed to consume the investigational product at least 2 h prior to or after taking any medication.

For the first 2 weeks, participants will go through a run-in period, where they will all receive the cornstarch control. During weeks 3 to 12 (period 1), participants will receive either RPS or cornstarch. The first treatment received will be determined by a randomization procedure. During weeks 13 to 16, participants will undergo a washout period where they will all consume cornstarch. During weeks 17 and 26 (period 2), participants will receive the treatment they did not previously consume (RPS or cornstarch, respectively).

Participants will complete questionnaires and food records at the beginning and end of each treatment period (Table 1). They will also provide blood, urine, and faecal samples for analysis (Table 1).

**Table 1 Tab1:** The schedule of enrolment, interventions, and assessments

Assessment	Screening and enrolment	Visit 1	Visit 2	Visit 3	Washout	Visit 4	Visit 5
Periods		Run-in		Period 1		Period 2	
Day in study		1	15	84	85–112	113	182
Informed consent	□						
Screening	□						
Demographics	□						
Medical history anthropometrics	□	□	□	□		□	□
Dietary recalls			□	□		□	□
SF-36, ESAS			□	□		□	□
Blood, urine, and stool collections			□	□		□	□
Adverse event			□	□		□	□

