#### Exclusion criteria

The participant may not enter the trial if any of the following apply: the participant is cognitively impaired and cannot give consent or participate in the group programme; the participant has an existing relationship with the research team, such as supervisory relationship (student, employee) or familial relationship (child, spouse, etc.); participants who indicate that they cannot consume study treatments; participants who indicate they are allergic to potatoes or corn; female participants who are pregnant, lactating, or planning pregnancy during the trial; history of renal transplant, ongoing dialysis, use of antibiotics (last 3 months), bowel diseases, cancer, surgically removed bowel, or any gastrointestinal surgery (e.g. intestinal resection, gastric bypass, colorectal surgery); inability to consume treatment due to swallowing or GI issues; participating in another interventional trial that could influence the intervention or outcome of this trial; participants with uncontrolled diabetes with A1C > 10%; participants who consume probiotic supplements; participants with abnormal constrictions of the gastrointestinal tract, diseases of the oesophagus, and/or the superior opening of the stomach (cardia), potential or existing intestinal blockage, paralysis of the intestine, megacolon, faecal impaction, appendicitis, a sudden change in bowel habits that has persisted for more than 2 weeks, undiagnosed rectal bleeding, or failure to defaecate following the use of another laxative product; participants with severe anaemia (haemoglobin less than 70); participants taking medications which inhibit peristaltic movement (e.g. opioids, loperamide); and participants able to maintain high fibre/adequate fibre intake through diet or taking other fibre supplements.

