### Compliance

Diaries with daily checklists for the 2 sachets will be given to the participants for each day during the run-in, washout, and treatment periods. These will be used to monitor their compliance with the study protocol. Additionally, participants will be instructed to return all empty sachets for counting purposes. Compliance for both groups will be defined as an attendance of ≥ 90% of the scheduled visits with the research team and ≥ 80% of the required treatments consumed according to diary entries and returned sachets. Participants will be monitored every week by the research team through phone calls or online videos. Additionally, there will be a study dispensing log which will be used to track all study treatments given to each of the participants. This log will include participant ID, date of dispensing, randomization code, and the returned sachet counts. Concomitant medication will be recorded at the end of the run-in and each treatment period.

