#### Ongoing assessments

Participants will be able to contact the study team at any time and will be given options to do so (text, voice call, video link, urgent in-person appointment). After enrolment in the study, participants will have follow-up virtual/in-person study visits as described in Table 1. Study visits will be acceptable on days within ± 5 days.

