#### Edmonton Symptom Assessment Scale (ESAS)

ESAS will be completed at the beginning and end of each period through paper or online by REDCap. The ESAS is a widely used tool for measuring physical and psychological symptom distress that has been validated in individuals with CKD [22], which consists of nine visual analogue scales (0–10 scale) for pain, activity, nausea, depression, anxiety, drowsiness, appetite, well-being, and shortness of breath. The scale for each symptom is anchored by the words “no” and “severe” at 0 and 10, respectively.

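### Adverse events are scheduled only at visits 69 days apart within each period, and neither the weekly contacts nor any described instrument asks about bowel symptoms, so transient gut intolerance may be missed

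*Protocol article*

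**What the plan says.** *Recording of adverse events* states that "all AEs occurring during the trial that are observed by the investigators or reported by the participant will be recorded on the CRF". An event need not be attributed to the product to be recorded. Each event carries start and stop dates, a severity grade and a relatedness judgement. No list of symptoms to be asked about is described.

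Table 1 has an AE row marked at Visits 2, 3, 4 and 5, which fall on days 15, 84, 113 and 182. *Ongoing assessments* adds: "Study visits will be acceptable on days within ± 5 days".

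*Compliance* says: "Participants will be monitored every week by the research team through phone calls or online videos". The sentence stands among the diary, sachet-count and dispensing-log provisions and does not mention AEs.

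*Exclusion criteria* lists many bowel conditions, among them impaction, possible blockage, undiagnosed rectal bleeding and "a sudden change in bowel habits that has persisted for more than 2 weeks". *Discontinuation/withdrawal of participants from trial treatment* names ineligibility that arises during the trial as a ground on which investigators may discontinue a participant.

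The ESAS section gives its nine scales as "pain, activity, nausea, depression, anxiety, drowsiness, appetite, well-being, and shortness of breath".

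**The concern.** The plan screens carefully for bowel problems at entry and then describes no question about them afterwards. Between scheduled assessments it depends on a participant choosing to raise a symptom, although a member of the team is due to speak to that participant every week.

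Two uses of the data are affected. The only external safety check is a single midpoint review of clinical chemistry and AEs by an outside nephrologist (*Safety monitoring committee*). A low AE count is hard to interpret there if nobody asked. The results are also meant to form the basis of a larger multicentre trial (*Discussion*), for which tolerability of the starch matters. The primary outcome, serum indoxyl and p-cresol sulphate, is not affected.

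**Working it through.** The article gives no figure for AE capture, so there is none to reproduce. The check uses the visit days in Table 1 and a comparison of the described instruments.

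**Intervals between scheduled AE assessments**

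- Period 1: 84 − 15 = 69 days.
- Period 2: 182 − 113 = 69 days.
- With ± 5 days at both visits: shortest 69 − 10 = 59 days, longest 69 + 10 = 79 days.
- Across washout (days 85–112): 113 − 84 = 29 days, with an assessment immediately before and immediately after.
- Run-in: 15 − 1 = 14 days.

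The first figure agrees with the text: "During weeks 3 to 12 (period 1), participants will receive either RPS or cornstarch". That is 10 weeks, or 70 days counted inclusively (84 − 15 + 1 = 70).

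**Contacts already planned.** If the weekly contact runs through all phases, there are about 182 / 7 = 26 contacts per participant and about 70 / 7 = 10 per treatment period. The scheduled AE assessments number 4. The sentence on weekly contact does not name the phases, so 26 is an assumption. The neighbouring sentence on diaries does cover run-in, washout and treatment.

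**What each described instrument asks**

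| Instrument | Gut content | When |
|---|---|---|
| ESAS | nausea, appetite, general pain; nothing on bowel habit, bloating or stool | days 15, 84, 113, 182 |
| SF-36 | bodily pain only | same days |
| ASA24 recall | diet, not symptoms | same visits in Table 1 |
| Daily diary | checklist for the two sachets | daily |
| Weekly contact | none described | weekly |

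**An illustration.** Suppose a bowel change starts on day 15, the start of period 1. It reaches 14 days on day 15 + 14 = 29, which is 84 − 29 = 55 days before Visit 3. In that interval it enters the record only if it is volunteered or noticed. This shows how long the schedule can leave such a change unasked about. It does not say how often that would happen.

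**At the midpoint review.** A participant who has just finished period 1 has had two scheduled AE assessments, days 15 and 84. The first closes the cornstarch run-in, so only the second follows randomised treatment.

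**The case against.** The strongest reply is that AE recording is continuous. Any reported AE is recorded with its dates. Participants may reach the team at any time by several routes (*Ongoing assessments*). A participant who reports an AE is offered an appointment within a week or at the next clinic, whichever comes first. The qualified investigator monitors AEs throughout (*Qualified investigator responsibilities*). A weekly call also gives a natural opening to mention a symptom. All of this stands: the four visits are not the only points of capture. But capture between them is passive, and mild, self-limiting gut symptoms are the ones people are least likely to volunteer.

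A second reply is that a condensed article may leave a call script or AE form to the full protocol. That is possible, and citing such a script would close the point. The article does, however, state an explicit AE schedule in Table 1 and assign the weekly contacts to compliance. Those stated choices are what is questioned here.

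A reader might infer four stronger things, none of which the article supports:

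- *That bowel harm is the main risk.* The exclusions rank no risk, and some may protect the microbiome outcome rather than flag harm. The article calls the interventions low risk and related AEs very unlikely. Bowel conditions are only the largest group listed.
- *That symptoms will be under-recorded, or unevenly between products.* No rate is given, and AE capture is described identically for both products under blinding.
- *That nothing touches the gut after entry, or that washout is uncovered.* The ESAS covers nausea, appetite and pain, and AE assessments fall on days 84 and 113, either side of washout.
- *That the exclusion and discontinuation sections conflict.* They do not, since the latter already provides for ineligibility that arises during the trial.

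**Conclusion.** The point holds as an inexpensive improvement to a stated schedule. It is not an error or a contradiction. Scheduled AE enquiries are 69 days apart within each treatment period (59 to 79 with the window), the existing weekly contacts are not linked to AE enquiry, and no described instrument asks about bowel habit, bloating or stool. Transient or mild gut symptoms may therefore be missed.

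The number missed cannot be computed from the article. The conclusion rests on two assumptions: that no symptom script for the weekly contacts exists in documents not shown, and that some participants will not volunteer minor symptoms.

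**What to change.** Add an AE enquiry to Table 1 at each existing weekly contact, in run-in, period 1, washout and period 2. Use the same short script in both periods: one open AE question, then a few fixed bowel items based on the plan's own exclusions (for example change in bowel habit and its duration, absence of stool, rectal bleeding), plus bloating and abdominal pain. Record the answers on the AE form, report the items by product, and include them in what the midpoint reviewer sees.

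The cost is a call script and a REDCap form, slightly longer calls, and more minor AEs to record in both periods. No visits or samples are added. How any such case is managed clinically stays with the sponsor and the qualified investigator under the existing exclusion, investigator-responsibility and discontinuation sections. No clinical rule is proposed here.
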